## Abstract

**Background:** People with severe mental disorders (SMDs) have higher disease and death rates than the general population. Stigma (negative attitudes and perceptions) contributes to limited access to health services and a lower quality of medical assistance in this population, and it is manifested as negative attitudes, social distance, and discrimination toward this social group. For these reasons, healthcare workers are a priority group for anti-stigma interventions. This study aims to assess the effectiveness of a program specifically designed to decrease negative attitudes and social distance and increase inclusive behaviors in healthcare workers toward people with SMD.

**Methods:** The study will be a randomized clinical trial. A minimum of 210 healthcare workers from 11 primary care centers in the province of Concepción, Chile, will be randomly chosen to receive the program or be part of the control group. There will be a pre-, post-, and 4-months evaluation of social distance, attitudes, and behaviors of participants toward people with SMD using standardized scales such as the social distance scale, which is a scale of clinician attitude toward mental illness adapted from attitudes of clinicians toward mental illness, and self-reports. The intervention program will consist of education strategies, direct, and indirect contact with people diagnosed with SMD, and skill development. There will be six face-to-face sessions directly with the participants and two additional sessions with the directors of each healthcare center. The program will involve a facilitator who will be a healthcare professional and a co-facilitator who will be a person diagnosed with SMD.

**Discussion:** This study will evaluate an intervention program especially designed to reduce stigma in healthcare workers toward people with SMD, a topic on which there is little background information, particularly in low- and middle-income countries. It is important to have interventions with proven effectiveness for this purpose to ensure equity in healthcare services.

**Trial Registration:** This study was registered under ISRCTN.com (ISRCTN46464036).

## Introduction

Several studies have shown that people with severe mental disorder (SMD) have higher morbidity, lower life expectancy, and higher mortality rates than the general population (1, 2). There is no consensus on the definition for SMD and on the specific disorders it comprises. However, in general, the criteria proposed by the National Institute of Mental Health (NIMH) in 1987, which continue to be used, are as follows: diagnosis of psychosis, duration of more than 2 years, and marked interference in daily functioning (3–5). Schizophrenia is often considered the prototype of SMD (6).

Studies have shown that people with SMD have a higher prevalence of hepatitis, osteoporosis, obstetric complications, cardiovascular diseases, obesity, diabetes, dental problems, and other chronic diseases compared to the rest of the population (7, 8). Furthermore, these results have been found in countries with different cultural backgrounds, including those in Latin America, such as Brazil (9–11). It has also been shown that people with SMD are less likely to receive adequate health care (12). Indeed, there exists an inequality in health care for this population compared to the general public, both in hospital care and primary healthcare service (PHS) (13). Hence, there is an interest in developing strategies to ensure equity in health care for people with SMD (14–16). Inequity in health care is a result of multiple factors, but the more unresolved one is stigma toward people with a diagnosis of SMD (17, 18). Stigma is currently understood as a relational process that includes cognitive, affective, and behavioral components. It refers to a social process of labeling, loss of status, and discrimination toward a person who has an attribute that is considered negative by their community (19). Self-stigma is one of the main consequences of stigma and is characterized by the loss of self-esteem and self-efficacy due to the internalization of public stigma. Living in a society that ascribes negative characteristics to people with SMD can lead them to internalize these ideas and think that they are less valuable because they have a psychiatric disorder (20). Moreover, self-stigma has other harmful effects because some people will not seek professional help or follow treatment for fear of being identified as “mentally ill” (21). Furthermore, self-stigma produces feelings of shame and anxiety in people with SMD that can increase their stress and affect their risk of relapse (22).

In health care, several studies indicated that healthcare personnel have prejudices, negative attitudes, and discriminatory behavior toward people with SMD (16, 23–25). For instance, a recent study comparing professionals at both PHS and secondary healthcare centers found that physicians and nurses at PHS had more negative attitudes toward people with SMD than their colleagues at secondary healthcare centers (26). Although stigma is similar in different professional groups such as nurses (27, 28), physicians (29), pharmacists (30), and psychologists (31), there seems to be some differences between them. For example, professionals closest to the area of social sciences, such as psychologists, would have less stigma than professionals in the area of healthcare, such as physicians and nurses (32). Despite the few studies on this topic in Chile, the results are in agreement with other published studies demonstrating that there are prejudices and negative attitudes toward people who have SMD (33, 34). It has been shown that stigma affects the inequity of health care in several ways. For instance, there is abundant evidence describing the effect of barriers to access healthcare services that makes it difficult for the affected people to request help (35, 36). In Chile, the lack of knowledge about mental disorders and stigma are the main reasons Chileans do not seek treatment (37). On the other hand, healthcare personnel mistakenly attribute physical signs and symptoms to a mental disorder, which leads to sub-diagnosis and inadequate treatment of physical health problems (16). Finally, a negative attitude toward the patient is associated with a lower adherence to treatment. Therefore, healthcare personnel should be considered a priority group for anti-stigma interventions, especially those working in PHS (38).

The area of anti-stigma interventions is a relatively new field. One of the models used to reduce stigma is the social-cognitive model (39). In this model, erroneous social beliefs (i.e., stereotypes) produce a negative attitude (i.e., prejudice) that leads to discrimination. The prejudice is based on various settings and previous biases that tend to favor the perception of the ingroup over that of the outgroup. In other words, everything that seems strange or alien to one's own perception tends to be categorized in a negative way. Thus, the intervention is focused on modifying stereotypes and attitudes to influence discriminatory behavior (40). For example, stereotype perception is modified by providing information that disproves previous concepts, and prejudices are reshaped by favoring processes of re-categorization to develop new ideas and attitudes. These processes are carried out through social interaction with the affected outgroup (41, 42). However, studies in this area show that giving information by itself does not assure a behavioral change, but that modification of the emotional response (prejudice) is more effective at getting people to act differently (43). The emotional change is easier to achieve through direct interaction with stigmatized people, thus the subject or situation that is alien or foreign becomes familiar and close.

Two major types of anti-stigma campaigns have been developed: generalized and localized. The first corresponds to mass campaigns developed from different strategies aimed at the general public (44). Among the most outstanding initiative in this area is the program “Open the Doors” (World Psychiatric Association) (42). Despite the benefits of this type of campaign, several researchers maintain that it has important limitations, such as: (i) little knowledge of the population, (ii) biases in the evaluation, and (iii) low efficiency to internalize what has been learned. Hence, other types of more localized or workplace interventions have been proposed as preferable alternatives. These initiatives are aimed at selected groups such as employers, schoolchildren, and healthcare personnel, among others; they have the advantage of being more intensive, so that although they reach fewer people, more work is done with the participants. On the other hand, it has been demonstrated that information against attitudinal learning is only assimilated in the context of where it is taught; thus, it is better to acquire it in places where it will later be used (45). For example, a recent review by Hanisch et al. (46) indicated that anti-stigma interventions in the workplace are the most effective at reducing stigma in the work environment. Programs in the workplace have been fundamentally based on two major strategies or components: education and contact. Education provides information about mental disorders to modify social stereotypes. For instance, specific aspects of SMD are discussed such as causes, risk factors, symptoms, and treatments (47). This education is useful if the transmitted information is discussed and real cases are presented. It is also necessary to establish the types of beliefs to be modified according to the particular diagnosis and the characteristics of the intervention group. This type of intervention is mainly done through conferences and debates (48). Furthermore, several studies have shown that knowledge about the subject makes people less likely to stigmatize and discriminate against this population (43, 49). This strategy has been one of the most utilized with healthcare personnel, and similar to what happens in the general population, the results indicate that imparting information decreases negative attitudes toward people with SMD; however, the duration of the changes is limited (50).

The other major strategy, contact with affected people, is limited to interventions in which a person with a mental disorder tells their experience to a specific group, either directly or indirectly through audiovisual media (48, 51). The conditions under which contact occurs are important for success. For example, the interaction should be cooperative, perceiving similar status, and not competitive. Indeed, the largest meta-analysis performed on the subject, which included 515 studies, determined that the conditions of contact raised by Allport contributed to diminishing prejudice; however, even if all conditions are not met, contact has a positive effect on decreasing stigma (52). For contact to be effective, it is important that people do not have behaviors and attitudes that are stereotypical of the SMD, and that they have the support of the directors of the Center where the intervention is carried out. Contact seems to be the best strategy to reduce stigma against people with SMD. In fact, several studies indicate that subjects who interact with people who have SMD are less likely to have negative attitudes toward them (53, 54). In a study performed in Chile on the perception that the general public and healthcare workers have toward people with SMD, it was found that those who had greater contact with people with SMD had less authoritarian and restrictive attitudes (55). Indeed, studies performed with healthcare personnel demonstrate that using direct contact with people with SMD is a strategy that decreases negative attitudes and social distance and increases acceptance toward this social group (23, 56, 57). However, the main limitation to developing this strategy is that it requires that people affected by a mental disorder be willing to publicly disclose their condition and talk about it. Despite this difficulty, studies suggest that the active involvement of those affected in these interventions increases their self-esteem and empowerment, which are fundamental for their recovery (54).

Intervention programs tend to use both strategies in different formats. Although there is evidence that education and social contact reduce prejudice toward people with SMD, it is unclear under what conditions each strategy would be more effective (44). In recent years, some research has shown that healthcare personnel have more negative attitudes toward people with SMD when they feel that it is difficult to interact with them and they are unable to contribute to their treatment (58, 59), which leads to frustration and rejection. Thus, assessments of anti-stigma programs recommend including skills training (60–62). For example, teaching healthcare personnel how to welcome and resolve difficult situations with those who have SMD and their families is a central factor in reducing stigma.

Intervention programs have been evaluated mainly through tests that measure people's knowledge and attitudes toward SMD, where knowledge tests indicate the level of information acquired by people post-intervention (63). With regards to attitudes, multiple scales have been used, the most common one being the Community Attitudes to Mental Illness (CAMI) scale (63). Social distance measures are also used to assess the willingness of someone to interact with a specific person in a specific type of relationship (64). These scales evaluate behavioral intention, so they are in some way between the evaluation of attitudes and behaviors. Therefore, these are used as a proxy measure for behavioral change. This is important since studies have pointed out that in addition to considering attitudes, one must also evaluate the behavior modification of participants in an intervention. Indeed, a behavioral change toward people with SMD would ultimately improve their quality of life (47). However, the main limitation of studies on anti-stigma interventions is that they used a pre- and post-test design without a control group. It was estimated that < 30% of studies used a control group, so the interpretation of their results for the intervention cannot be considered statistically valid (41, 44). In the last decade, some researchers have suggested that for an intervention to be successful, it is necessary to perform a qualitative evaluation before and after the intervention and to actively involve people diagnosed with SMD (47). This type of evaluation makes it possible to understand the nature of the stereotypes and prejudices of the group that one is going to work with. This would allow the implementation of an intervention relevant to the beliefs of the target group (40).

Regarding the participation of service users, an approach called “Research based on community participation” has been promoted for several years (65). This encourages the participation of affected people in their health care throughout the research process, both in the design of the interventions as well as in the execution and evaluation. Several studies point out that anti-stigma interventions should be performed from this perspective so that the programs respond to the needs of those affected while at the same time favor their recovery and empowerment (50, 63). Therefore, it is fundamental to reduce negative attitudes and discrimination in PHS personnel toward this social group. However, there is little international research on anti-stigma interventions with healthcare personnel, especially in developing countries (66). This is a relevant fact because context has an important role in the effectiveness of an intervention; in other words, cultural differences in attitudes toward people with SMD are crucial for the design of the intervention (47).

The present study trial seeks to evaluate a mixed intervention strategy for the reduction in stigmatization associated with SMD, particularly in people diagnosed with schizophrenia. To accomplish this, an intervention program will be designed, implemented, and evaluated. This program combines methods/techniques that have been shown to provide the best results in reducing stigmatization. The program will implement education, contact, and skills development as core strategies. We will actively work with people who have received a diagnosis of SMD. The objective is to design, implement, and evaluate an intervention program to reduce negative attitudes and social distance, and increase inclusive behaviors of healthcare workers toward people with SMD. The program will be implemented with healthcare workers from primary care centers. In Chile, the majority of the population use primary healthcare centers for medical attention in the public health system. Each center provides service to a specific number of inhabitants located in the population sector, and is equipped with a multi-professional health team, technicians, and an administrative support staff. The intervention program will be developed for all healthcare workers except the administrativ staff.

The hypotheses for this study are as follows:
Compared to the control group, healthcare workers in the intervention group will have less negative attitudes and social distance toward people with SMD (schizophrenia) in the post-test evaluation and follow-up.Healthcare workers in the intervention group will exhibit more inclusive behaviors toward people with SMD (schizophrenia) in the post-test evaluation and follow-up compared to the control group.

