#### Contact strategy

*Direct contact*: There is direct contact throughout the program because the co-facilitator is someone who has a diagnosis of SMD. In one of the sessions, another person with a diagnosis of SMD shares their life testimony.*Indirect contact*: This is initiated through (i) *videos* in which the participants watch and analyze short videos that show different experiences of people with SMD. The videos show situations of stigma and discrimination that those affected have experienced (with health personnel present), as well as good experiences that have happened to them in the context of their health care; (ii) *written cases* that provide information about a person who has received a diagnosis of SMD for the group to discuss; and (iii) *skills strategy* that teaches skills in a practical and contextualized way on how to accept and resolve difficult situations when dealing with people with SMD. This is performed through role play with real cases that have occurred in the healthcare center. Additionally, verbal and non-verbal communication is addressed.

The sessions are designed to encourage group reflection. The information presented will be discussed and analyzed in groups in a way that favors dissonance and cognitive categorization. Furthermore, the program incorporates effective implementation of non-stigmatizing practices through the planning and execution of behaviors that increase positive attitudes and respectful and inclusive treatment toward people who have SMD (47). The program format emphasizes contact conditions that favor its effectiveness, i.e., status equality between the participants, achievement of common goals, and establishment of a cooperative relationship (52). Furthermore, the contact strategies focus on favoring empathy, which is inversely related to prejudice.

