### Measurements

#### Social Distance Scale (SD)

Social distance scale (SD) Link et al. (73). This scale evaluates the social distance that people have toward people with SMD. It is composed of a brief vignette where the case of a person with SMD is revealed followed by seven items in a Likert-type response with five alternative answers ranging from disagree to completely agree. The questions are related to different situations that vary in the degree of closeness to the affected person who could be a neighbor, friend, employee, or partner. This scale was adapted and validated for use in the Chilean population (74). The final questionnaire is composed of two factors: “closeness and social interaction” (three items) and “intimacy and trust” (two items). The internal consistency of each of the factors reached Cronbach's alpha values of 0.82 for factor 1, 0.75 for factor 2, and 0.78 for the total scale.

CAMI scale (75). This scale evaluates the attitudes of the general public toward people with SMD. The response is a Likert-type format that is based on five alternatives that range from totally agree to totally disagree. The original scale was adapted and validated for use in the Chilean population (76). The scale is made up of two factors, “acceptance” and “rejection of the installation of mental healthcare centers in the community,” each composed of five items. The internal consistency for each of the factors reached Cronbach's alpha values of 0.61 for the first factor, 0.66 for the second factor, and 0.69 for the total scale.

“Mental Illness: Clinicians' Attitudes” (MICA) scale (77). MICA is a 16-item scale that evaluates the attitudes of professionals and students working in health toward people with SMD. The questionnaire consists of six answer options in a Likert format that ranges from strongly agree to strongly disagree. The internal consistency of the original scale was good (α = 0.72). An adaptation of this scale is being made for validation in the Chilean population.

Self-registration of inclusive behaviors: This is an *ad hoc* scale created to assess self-perception of behaviors that one had toward the last person diagnosed with SMD with whom they had contact. There are 18 items with four response options in a Likert format.

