**STIGMA IN PRIMARY HEALTHCARE WORKERS TOWARD PEOPLE WITH DIAGNOSIS OF SEVERE MENTAL DISORDERS (SMD)**				
Attitudes of the general public toward people with SMD	Community Attitudes to Mental Illness (CAMI) scale	✔	✔	✔
Attitudes of professionals and students working in health toward people with SMD	Mental Illness: Clinicians' Attitudes (MICA) scale	✔	✔	✔
Social distance that people have toward people with SMD	Social distance scale (SD)	✔	✔	✔
Self-perception of behaviors that one had toward the last person diagnosed with SMD with whom they had contact	Self-registration of inclusive behaviors	✔	✔	✔

*T1, assessment before intervention; T2, assessment after intervention; T3, follow-up 4 months after assessment T2*.

Workers assigned to the control group will receive the program once the implementation is completed and the post and follow-up evaluations are finished. A minimum of 11 centers are needed to obtain the required sample size (Table 1).

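### The aim and Hypothesis 2 claim behaviour that workers show, but the only behaviour measure is a self-perception scale, so a difference supports a claim about self-reported behaviour only

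*Protocol article*

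**What the plan says.** **The claim.** The objective in the Introduction of the Protocol article is, among other things, to "increase inclusive behaviors of healthcare workers toward people with SMD". Hypothesis 2 turns this into a comparison with control: "Healthcare workers in the intervention group will exhibit more inclusive behaviors toward people with SMD (schizophrenia) in the post-test evaluation and follow-up".

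**The measure.** Under Measurements, the instrument for self-registration of inclusive behaviours was made for this study and is described as a "scale created to assess self-perception of behaviors that one had toward the last person diagnosed with SMD with whom they had contact". It has 18 items with four response options. In Table 1 it is the only behaviour row, assessed at T1, T2 and T3 and described in the same terms: "Self-perception of behaviors that one had toward the last person diagnosed with SMD with whom they had contact". The table lists no observer, service-user or record-based measure.

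**The setting.** Randomization is individual within each centre, and controls receive the program only after all evaluations are complete (Design; Procedure). The Contact strategy section says the program includes "planning and execution of behaviors that increase positive attitudes and respectful and inclusive treatment toward people who have SMD". It also says that a co-facilitator with an SMD diagnosis is present throughout, and that another person with SMD gives testimony in one session. T2 falls within three weeks of the program's end, and T3 is the four-month follow-up.

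**The stated limitation.** The Discussion names contamination between arms. It does not mention self-report.

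**The concern.** Behaviour that a worker shows to a patient and behaviour that the worker believes he or she showed are different quantities. The aim and Hypothesis 2 are worded as the first, and the instrument measures the second.

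The gap matters because the rating process can itself differ by arm. Workers in one arm have been trained in inclusive treatment and the others are waiting for that training. The training could raise self-ratings because workers now know what is valued. It could lower them because workers judge their own past conduct more strictly. Either can happen with conduct unchanged.

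A second difference lies in the item stem. It asks about the last person with SMD met, and only the intervention arm meets such people through the program before T2 and T3. The person rated could be a program contact in one arm and a patient in the other.

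At stake is the conclusion. Read as worded, a positive result would be reported as changed conduct in care.

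**Working it through.** **1. Claim against measure.**

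| Element | Where | What it refers to |
|---|---|---|
| Objective | Introduction | Inclusive behaviours of workers |
| Hypothesis 2 | Introduction | Behaviours that workers exhibit |
| Self-registration scale | Measurements; Table 1 | Workers' perception of their own behaviour |
| Social distance scale | Introduction; Measurements | Behavioural intention, self-completed; belongs to Hypothesis 1 |

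No row supplies behaviour seen by anyone other than the worker.

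**2. What the arm difference estimates.** Write the mean difference on the scale as

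observed difference = B + R,

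where B is the effect on behaviour and R the effect of the program on self-rating at unchanged behaviour. Randomization and the pre-test covariate deal with reporting tendencies present at baseline. They do not remove R, because R arises after randomization and through the program. With one self-completed measure, B and R cannot be told apart.

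**3. The plan's own sample size.** Inputs from Power and Data Analyses: d = 0.5, power 95%, significance level 5%, 105 per group. Two-sided testing is assumed because the article does not state it.

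- Normal approximation: n = 2(1.960 + 1.645)² / 0.5² = 104 per group.
- Two-sample t-test: 104.93, so 105 per group. The stated figure reproduces.
- Power at 105 per group and d = 0.5 (normal approximation): 0.952.

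**4. What that size means here (illustration only).** The standard error of the standardized difference is √(2/105) = 0.138, so a difference of 1.96 × 0.138 = 0.27 SD is significant. This is a simple two-group comparison. It ignores the gain from the pre-test covariate, which would lower the threshold. The values of R below are assumptions; the documents give none.

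| Assumed R (SD), with B = 0 | Chance of a significant difference |
|---|---|
| 0.1 | 11% |
| 0.2 | 30% |
| 0.3 | 58% |
| 0.4 | 83% |
| 0.5 | 95% |

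The opposite sign matters equally. If B = 0.5 and R = −0.2, the observed difference is 0.5 − 0.2 = 0.3 and the power falls from 95% to 58%. More participants would not help, since they sharpen the estimate of B + R and not of B.

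**5. The person rated.** Between T1 and T3 the intervention arm meets a co-facilitator with SMD at the program sessions and a further person giving testimony; the control arm meets neither. Nothing in the scale's description excludes these people from being the last person met. The issue is most direct at T2, but it can persist to T3 for a worker with no later contact.

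**The case against.** Self-report is not hidden. The Abstract mentions self-reports, the instrument's name says self-registration, and Measurements and Table 1 both say self-perception. Stating a hypothesis as a construct and defining its measure in Methods is normal practice. Leaving out observers or patient reports is a common feasibility choice. All of this stands, and it means the defect is in the wording of the claim and not in concealment. It does not qualify the aim or Hypothesis 2, which carry no such limit.

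A reader might infer that the protocol breaks its own rule, since the Introduction says "one must also evaluate the behavior modification of participants in an intervention". The text does not support that. The same paragraph places social distance between attitudes and behaviour and says "Therefore, these are used as a proxy measure for behavioral change". It accepts a self-completed proxy and sets no standard of observed behaviour.

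A reader might also infer that workers are taught the answers. The 18 items are not shown. Only overlap between the program's content and the construct is documented, and recency fits T2 better than T3. Lack of blinding is likewise an inference from the delayed-program design, though a safe one.

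Finally, the Discussion's remarks on policy and equity are general and hedged. They do not rest on this scale.

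**Conclusion.** The point holds as a mismatch between claim and measure. A difference on the self-registration scale would support the statement that trained workers report more inclusive behaviour. It would not show that they behave more inclusively.

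It would go too far to say that Hypothesis 2 can yield no conclusion, because the self-reported version remains fully testable. It would also go too far to attach a bias to the trial. One could assume items scored 1 to 4 and a shift of one category on four items, which gives 4 points, or d = 0.67, 0.50 or 0.40 for a total-score SD of 6, 8 or 10. Every input to that beyond the item and option counts is assumed. The size and direction of any reporting shift are unknown.

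The documented size is the threshold: about 0.27 SD is enough for significance with 105 per group, from whatever source. The conclusion rests on two inferences: that participants know their arm, and that a program contact could be taken as the last person met.

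**What to change.** 1. In the aim, Hypothesis 2 and the planned conclusion, replace inclusive behaviours with *self-reported inclusive behaviours*.
2. Add a sentence to the Discussion's limitations: the scale is completed by participants who know their arm and, in one arm, were trained in what it rates, so a positive result is not evidence of observed behaviour change.
3. Add one line to the scale's instructions, identical in both arms and at T1, T2 and T3: people met through the program do not count as the person to be rated.

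The cost is a narrower claim and one line in the questionnaire. A worker whose only recent contact came through the program will have to rate an older one. Sample size, visits, staffing and analysis do not change.
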